### Outcomes

#### Primary and secondary outcomes

The primary outcome of the study is percentage change in cervical cancer screening uptake from baseline to follow-up in the intervention group compared to the control group in a 12-month home-based health education intervention. The baseline survey will be conducted before the cluster randomization, and a follow-up survey of similar method will be conducted after 12-month intervention. The response of each participant for cervical cancer screening in the baseline survey and the follow-up survey will be compared to evaluate the percentage. In addition, FCHV will provide a referral slip to the participants in the intervention group (keeping a copy of the referral slip to submit to the field supervisor) during the home visit, which they take with them and submit to the health facility for VIA screening. The referral slip contains study code, name, age, address, and signature of both FCHV and the participant. FCHV will inform the participants about the health facility where the services are freely available. The key health personnel providing the VIA screening services are oriented about the study. Furthermore, confidentiality about the participants’ information will be maintained throughout the intervention. The field supervisor will collect the referral slip to confirm that the participants have received VIA screening and results from all the health facilities of the intervention ward as a reference to the participants’ response.

The secondary outcomes of the study are change in the level of knowledge and awareness among women on cervical cancer screening and prevention. The response of each participant for knowledge and awareness on cervical cancer screening in the baseline survey and the follow-up survey will be compared to evaluate the change using the validated questionnaire [19, 20].

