### Data analysis

STATA version 15 software (StataCorp, College Station, TX, USA) will be used for quantitative analysis following the Consolidated Standards of Reporting Trials (CONSORT) guidelines for cluster-randomized trials. Flowcharts (Fig. 1) will include the number of participants seen at each stage of the trial, eligible, randomized, and analyzed for the primary outcome. In the initial analysis, we will compare baseline characteristics of enrolled participants in the study arms and follow-up status. We will use mixed-effect logistic regression to compare between the groups as the outcome (the primary outcome would be the difference in the proportion of women who participate in the cervical cancer-screening program between intervention and control within 1 year). Comparison of the knowledge scores between baseline and follow-up, after 1-year intervention, will measure the knowledge level. Estimation will take into account the effect of potential confounders (age, ethnicity, education, parity, income, location, etc.).

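### The only comparison stated for the secondary knowledge outcome is baseline versus follow-up; the intervention-versus-control contrast should be written in.

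*Protocol article*

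**What the plan says.** The protocol article treats its two outcomes differently.

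- **Primary outcome (screening uptake).** Under Primary and secondary outcomes it is a change "from baseline to follow-up in the intervention group compared to the control group". Under Data analysis it has a model: "We will use mixed-effect logistic regression to compare between the groups as the outcome". A parenthesis in that sentence ties the model to the proportion of women screened within one year.
- **Secondary outcome (knowledge and awareness).** It is defined without reference to the arms: "The secondary outcomes of the study are change in the level of knowledge and awareness among women on cervical cancer screening and prevention". Responses "in the baseline survey and the follow-up survey will be compared to evaluate the change using the validated questionnaire". The Data analysis section then adds its only sentence on knowledge: "Comparison of the knowledge scores between baseline and follow-up, after 1-year intervention, will measure the knowledge level".

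Two general statements stand around that sentence. The analysis is to be done "following the Consolidated Standards of Reporting Trials (CONSORT) guidelines for cluster-randomized trials", and "Estimation will take into account the effect of potential confounders (age, ethnicity, education, parity, income, location, etc" follows directly after it.

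**The concern.** A baseline-to-follow-up difference measures everything that happened over the year, not only the intervention. The article itself points to other sources of change. The same women are surveyed twice by a similar method. Government screening education continues as usual care (Interventions). The trial runs inside a community non-communicable disease programme dating from 2014 (Sample size calculation). Any of these could raise scores in both arms.

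The randomized control arm is there to remove such common change. If the knowledge sentence were followed as written, the contrast that does this would not be estimated, and a rise in the intervention wards could not be interpreted as an effect of the volunteers' home visits. This is more than a detail left to an analysis plan: the article does name a comparison for knowledge, and an analysis plan that copied it would carry the gap forward.

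**Working it through.** **1. What contrast is available for knowledge.** The knowledge sentence does not say whether it applies to intervention women, to each arm separately or to all women pooled. None of these readings gives a difference between arms. The mixed logistic model does give one, but it is attached to a yes/no screening outcome and does not carry over to a score. The CONSORT statement names no contrast. The confounder list includes location but neither arm nor a ward effect.

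**2. Are the data there?** Yes. Both surveys precede or follow the intervention in the whole trial population, and the Interventions section refers to a 12-month assessment of control women. A randomized comparison of knowledge needs nothing new.

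**3. The plan's own figures.** None is given for knowledge: no SD, ICC, expected change or power. The only power statement (seven wards per arm, 49 women per ward, ICC 0.01, 20% loss, 90% power) concerns uptake. It reproduces closely if one assumes 5.4% control uptake (the background figure for ages 30–65), a 10-point difference and two-sided alpha 0.05. That needs 194 women per arm before clustering; solving 7m = 194[1 + (m − 1) × 0.01] gives m = 38.0 analysed per ward, and 38.0/0.8 is about 47.4 recruited. This point does not depend on it.

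**4. Illustration of the literal reading.** Assumptions: no intervention effect, the same rise in both arms, correlation 0.5 between the two scores, and ICC 0.01 borrowed from the uptake calculation.

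- Intervention women analysed: 277 × 0.8 = 221.6, or 221.6/7 = 31.7 per ward.
- Design effect: 1 + (31.7 − 1) × 0.01 = 1.307.
- SE of mean change: sqrt(2 × (1 − 0.5) × 1.307/221.6) = 0.077 SD.
- Rise 0.1 SD: z = 1.30; probability of significance Φ(1.30 − 1.96), about 26%.
- Rise 0.2 SD: z = 2.60; about 74%.
- Rise 0.3 SD: z = 3.91; about 97%.

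A separate simulation (4,000 runs, 39 women in each of seven wards per arm, SD of change 1, ICC 0.01) made no allowance for wards in the before-after test:

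| Common rise (SD) | Before-after, wards allowed for (formula) | Before-after, wards not allowed for (simulation) | Between arms, ward means (simulation) |
|---|---|---|---|
| 0 | 5% | 9% | 5% |
| 0.1 | 26% | 40% | 5% |
| 0.2 | 74% | 88% | 5% |
| 0.3 | 97% | 99% | 5% |

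The two before-after columns differ in sample size as well as in ward handling. The formula column already allows for wards, so its false positives come from the missing control contrast, not from clustering.

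**5. Why the fix should also name the wards.** In the same simulation, a between-arm test of change that ignored wards rejected in 8–10% of trials at ICC 0.01 and in 23–25% at an assumed ICC of 0.05. The ward-level test stayed between 4.2% and 5.4%.

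**The case against.** The best defence is that the knowledge sentences describe how each woman's outcome is obtained, not the test. The outcomes section uses nearly the same wording for the primary outcome, where each participant's baseline and follow-up responses are also compared, and that outcome is explicitly between arms. Other text points the same way. The analysis sits under CONSORT for cluster trials. Adjustment for stable characteristics such as ethnicity has an obvious role between arms and little within women. The contamination section promises adjustment when estimating the effect and does not limit this to uptake.

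This stands as evidence of intent, and it rules out stronger readings. A reader might infer that the plan discards the control arm, ignores the wards and will credit any within-arm rise to the volunteers. The article says none of these things. No text confines the knowledge comparison to the intervention arm or proposes a within-arm significance test. That wards are ignored is inferred from silence, and the model for a secondary outcome is something a condensed article may leave to the full plan.

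What the defence does not do is supply the contrast. For the primary outcome the per-participant sentence is accompanied by an explicit comparison with control and a between-group model. For knowledge, the Data analysis section repeats the time comparison and stops.

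**Conclusion.** The point holds as a correction to the wording of a secondary outcome. The stated comparison for knowledge is baseline versus follow-up, with no between-arm contrast, and taken literally it cannot separate the intervention from common change over the year. The intent may well be better than the text.

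The article gives nothing from which to estimate the actual size of the problem. The 74% and 97% figures rest on an assumed rise of 0.2 to 0.3 SD, an assumed correlation, a borrowed ICC and a test confined to the intervention arm that the article does not specify. They show that a modest common rise would suffice to mislead; they do not predict this trial's error rate. The logic does not depend on them. The primary outcome is not affected. The correction should be made, but the trial's main conclusion does not hang on it.

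**What to change.** Replace the knowledge sentence with one stating that knowledge and awareness at follow-up, adjusted for baseline score (or change in score), will be compared between intervention and control arms with an analysis that accounts for the 14 wards. The result is reported as the between-arm difference with a 95% CI. Suitable analyses include a mixed model with a ward random effect and a small-sample correction, or a ward-level analysis. The choice between these, and between baseline adjustment and change scores, can be left to the analysis plan; since the article does not describe the scale of the score, the model should be matched to it. Within-arm changes can still be shown, as description only. Align the matching sentence under Primary and secondary outcomes.

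The cost is a sentence in each place; the data are the same. The article puts the end of endpoint assessment at the end of August 2021, so on its own timetable the clarification could be made and dated before the final analysis.

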## Interim analyses and stopping rules

There is no plan for interim analysis, as we do not expect a situation that would lead us to stop the study. However, in the event of an extreme situation such as a natural disaster, a conflict, or duplication of similar interventions in our control area, we will temporarily stop the study to assess the implications on the study design.

## Trial management

We have a robust mechanism to ensure data quality. At first, the data enumerators will receive intensive training on the process of data collection. The principal investigator will monitor the data enumerators on a day-to-day basis. The research assistant assigned for data entry will inspect the data manually and enter the data in EpiData software file (EpiData Association, Odense, Denmark). Double entry for 10% of the data will qualify potential errors in data entry quality. The research officer will crosscheck the data quality on the spot and in our field office for any incomplete, inconsistent, and invalid data. Any deviation in the data quality will require recollecting in the field.

## Indemnities

The study carries minimal risk to the study participants, which is why we have no compensation or insurance plan for the participants. However, we will provide medical insurance and US$5 per home visit to FCHVs for transportation expenses.

## Publication plan

The results of the trial will be published in a peer-reviewed journal.

## Discussion

The COBIN-C study is the first investigation of a community-based intervention to increase cervical cancer screening uptake in Nepal. We expect that a community-based, culturally tailored education intervention delivered by community health workers such as FCHVs will play a key role in increasing cervical cancer screening uptake in the study area. Indeed, community health workers can play an important role in understanding the cultural barriers including community health practices, cultural identity, and coping practices that can promote positive health outcomes [27].

Furthermore, studies from Iran, Kenya, and Nigeria have reported health education interventions and behavior change frameworks provide an effective base for cervical cancer prevention [23, 28–30]. In our study, FCHV in the intervention group will make three home visits to educate and empower women for cervical cancer screening uptake that is available free of cost at the local health facilities. Previous study reveals that appropriate and structured training program motivates FCHVs to contribute in addressing non-communicable diseases [14].

The health promotion package is a simple, feasible, and potentially effective approach. It may contribute in the implementation of the National Cervical Cancer Screening and Prevention policy and help reduce cervical cancer mortality in the long term in Nepal and if successful may be adapted to similar settings elsewhere.

## Trial status

The trial is now closed to participant accrual, but the trial is ongoing. The endpoint assessment of all the participants will be completed by the end of August 2021. The schedule of enrollment, interventions, and assessments is presented in Table 2. The protocol has been submitted for publication after the end of recruitment due to manuscript preparation and author’s travel plan.

**Table 2 Tab2:** Schedule of enrolment, interventions, and assessments

	Study period						
	Enrolment	Allocation	Post-allocation				Close-out
Timepoint (months)	***3***	1	***1***	***4***	***4***	***4***	***2***
**Enrolment:**							
**Eligibility screen**	**x**						
**Informed consent**	**x**						
***Informed consent with FCHVs***	**x**						
**Allocation**		**x**					
**Interventions:**							
***Training of FCHVs***			**x**				
***Home visit by FCHVs***				**x**	**x**	**x**	
**Assessments:**							
*Baseline variable* *Socio-demographic (age, education, ethnicity, monthly income, marital status), pregnancy, sexual, and reproductive characteristics*	**x**						**X**
***Outcome variable*** *# of women screened for cervical cancer*	**x**						**X**

The protocol version number and date—V1, 28 December 2020.

## Data Availability

Data set and informed consent forms will be available upon reasonable request to the corresponding author [name].

## Abbreviations

cRCT: Cluster randomized controlled trial
FHD: Family Health Division
FCHVs: Female community health volunteers
LMICs: Low- and middle-income countries
UNFPA: United Nations Population Fund
WHO: World Health Organization
